## Abstract

**Clinical trial registration:**

[ClinicalTrials.gov], identifier [NCT05031598].

## Introduction

The health-promoting effects of long-term fasting (LF), lasting more than 4 days and up to several weeks, are increasingly documented (1–3). Our group has shown that LF improves cardiovascular (CV) risk factors such as hypertension even in medicated subjects, lipoprotein distribution, non-alcoholic fatty liver symptoms, inflammatory parameters, oxidative stress, and gut microbiota profiles (4–9). A large observational study of 1,422 subjects underlined the safety, tolerability, and therapeutic efficacy of LF from 4 to 21 days (10). However, the precise physiological consequences of acute LF periods and subsequent food reintroduction phases are still not comprehensively understood.

A key molecular mechanism of fasting-mediated health benefits is the metabolic switch from glucose, as the main energy source, to the utilization of fat-derived lipids and ketones (11). During the first 48 fasting hours, the initial glycogen depletion is accompanied by fat and–to a lesser extent–protein utilization. The proportion of protein usage then decreases after the activation of protein-sparing mechanisms (12). In the 1980s, concerns about protein loss–and subsequent muscle decline–were raised for zero-calorie diets lasting more than 100 days, based on nitrogen balance measurements (13, 14), while the origin of protein breakdown was not determined. Conversely, in a recent study investigating 10 days of fasting, including daily moderate physical activity in 16 healthy men, muscle strength (grip and leg strength) was observed to be maintained and even increased (15).

Due to substrate mobilization in several metabolically active tissues, the size and weights of organs changes. Liver, spleen, kidneys and skeletal muscle mass decrease in rats after long periods of severe 50% calorie restriction (CR), while the brain and testes seem unaffected (16). Multiple cycles of fasting-mimicking-diet (FMD; 10% of normal daily calorie intake) in mice restored insulin-generating β-cells, promoted stress resistance, self-renewal division of stem cells, and hematopoietic lineage-balanced regeneration (17–19). Few clinical studies of long-term CR are available in humans. A 12-week semi-starvation intervention in 32 men reduced the heart’s overall size proportionally to the body weight and showed a trend of recovery after food reintroduction (20). Fat loss plays a role in the shrinkage of organ volume. After a 10-day fast in men, enhanced lipid oxidation was shown in muscles (15).

Furthermore, fasting-induced autophagy and apoptosis are also thought to contribute to organ shrinkage (21). Decreased protein content during fasting is restored upon food reintroduction, as documented by the switch to a positive nitrogen balance (22, 23). Consequently, organ size can be rebuilt due to *de novo* synthesis and stem cell activation, possibly conferring beneficial effects on tissue functionality. To the best of our knowledge, no extensive human studies exist that systematically analyzed the body composition after a LF period using state-of-the-art magnetic resonance imaging/spectroscopy (MRI/MRS) approaches. One case report outlined the effects of a 14-day fasting period in a healthy man by MRI/MRS, showing changes in adipose tissue distribution and fatty acid composition in multiple organs (24).

Thus, in addition to body and organ composition, we will investigate lipid metabolism during LF. Serum triglycerides, low-density-lipoprotein (LDL) and atherogenic subfractions (e.g., small dense LDL) significantly decreased after 2 weeks of fasting, pointing to a reduced lipid-associated atherogenic risk (9). Of note, high-density lipoprotein cholesterol (HDL-C) is inversely associated with both CV disease and mortality (25) and pharmacological interventions aiming at raising HDL-C levels were not successful thus far (26, 27). Hence, there is an increasing interest in measuring high-density lipoprotein (HDL) function, as reflected by cholesterol efflux capacity (CEC) and the serum cholesterol loading capacity (CLC), which are both indices of CV risk (28, 29). This study will investigate whether LF influences the reverse transport of cholesterol from the periphery to the liver. In addition, erythrocyte membrane fatty acid composition reliably predicts total mortality and clinical events (30–32). Therefore, we will determine the fatty acid composition of erythrocytes and the omega-3/omega-6 ratio during LF.

The exact cascade of molecular mechanisms leading to therapeutic benefits of different fasting regimes remains elusive, at least in humans (33). Interestingly, organisms maintain cellular and organismal homeostasis during fasting, *inter alia*, by well-orchestrated biochemical and (epi) genetic mechanisms (11, 34). The progress of precision metabolomics technologies recently opened new avenues to study the changing metabolic landscape during the fasting state in a spatiotemporal manner (35). Thus, this study will shed light on the intracellular metabolic consequences of LF in peripheral blood mononuclear cells (PBMCs), focusing on lipids and polyamines, which are essential for diverse cellular functions (36). Another aspect of LF-induced metabolic effects is increased endogenous hydrogen sulfide (H2S) production, a physiological gasotransmitter (37, 38) *via* sulfhydration/persulfidation (39) with health-promoting properties (REF). In mice, 40% dietary restriction increased H2S levels, which is required for the geroprotective effects of CR (37). Thus, we will investigate the impact of LF on H2S-mediated signaling in humans.

Finally, we will explore gut microbiota changes during LF. LF does not eliminate the gut microbiota, but elicits profound changes in its composition (6, 40). In our recent study, changes in bacteria profiles caused by fasting were associated with serum glucose and fecal branched-chain amino acids (6), suggesting that the gut microbiota can influence fasting-induced changes in energy metabolism. A more recent study even identified a bacteria which abundance correlates with serum concentrations of 3-hydroxybutyrate (41).

In light of these incognita, we designed a multi-stage single-arm interventional trial to apply state-of-the-art methods to elucidate the fasting-induced changes in metabolism, body composition, organ size and function, and the gut microbiome (Figure 1).

**FIGURE 1 F1:**
[figure not shown]
Main outcomes of the GENESIS study. By pooling knowledge acquired by macroscopic multi-organ fat distribution and composition provided by magnetic resonance imaging (MRI), with erythrocyte fatty acids, lipoprotein, peripheral blood mononuclear cell (PBMC) metabolome, protein persulfidation, and gut microbiome profiles, we aim to gain a deeper comprehension of molecular and physiological changes during fasting and food reintroduction.

## Methods and analysis

### Aims

First, the GENESIS study aims to document changes in body composition and the contribution of the main metabolically active tissues (skeletal muscular tissues, adipose tissues, liver, heart, spleen, kidneys, and brain) to the metabolic switch during a 12-day fasting period. Changes in the size and mass of organs will be quantified. We hypothesize that a re-expansion and regeneration will follow a transient decrease of organ volume during fasting up to 4 months after food reintroduction. Protein resynthesis upon food reintroduction might correspond to an acceleration of the physiological protein turnover, which will be evaluated by measuring nitrogen excretion. Additionally, the organs’ specific compositions, especially the fat components, and their function will be documented along the fasting process. We hypothesize that these multi-system changes are safe, and that they could also be reflected by an improved cardiac and skeletal muscle metabolism and mitochondrial oxidative capacity which will be investigated by spiroergometry.

Second, the study focuses on fat storage, function, and exchange in adipose tissue, liver, spleen, kidney, and splanchnic tissue. Among the lipids studied, we focus on cholesterol metabolism during fasting, particularly sub-types of HDL, but also CEC and fatty acid profiles in the erythrocyte membrane.

Third, we will measure PBMC metabolome profiles to reveal cellular metabolic changes in circulating, easily accessible immune cells.

Fourth, we will determine whether persulfidation, which contributes to the maintenance of cellular oxidative functions, changes during fasting.

Last, we will measure if various metabolic and physiological changes, as described above, correlate to individual gut microbiota profiles. The composition and function of the fecal microbiota will be evaluated during LF using shotgun metagenomics. This will help us understand how intestinal microorganisms are linked to human physiology during fasting.

### Study design

The GENESIS study is a prospective, monocentric, single-arm interventional study using a two-stage design. A total of 100 subjects will be included (Figure 2). The first 32 participants will undergo an augmented examination plan, including MRI/MRS scans to evaluate body composition changes at four time points: prior to and at the end of 12 fasting days, 1 and 4 months post fasting. This sub-cohort is statistically powered for detecting changes in whole body composition. Sixty-eight additional subjects will then be included for gut microbiota and lipid profile analyses. The study follows the STROBE guidelines (42).

**FIGURE 2 F2:**
[figure not shown]
Study design. Specific sessions for the subjects enrolled in the first stage of the projects are indicated in blue. The estimated numbers of volunteers needed to recruit the sample size of 100 subjects are indicated in gray.

### Recruitment

The study site is a specialized center for long-term therapeutic fasting under medical supervision. Detailed information about the GENESIS study will be provided orally and in a written manner to potential participants. For the recruitment of the first phase (32 participants), participation calls will be distributed in the study center, on social media channels of the Buchinger Wilhelmi clinic and in institutions working on fasting and nutrition. Informed consent will be collected prior to the start of the fasting period and any baseline measurements. Since participants of the first stage need to be physically present at four time points (prior and post fasting, follow-up visits after 1 and 4 months), they will stay at the Buchinger Wilhelmi clinic without charges. The remaining 68 participants will be recruited prospectively during 1 year from the regular pool of customers voluntarily undergoing fasting in the Buchinger Wilhelmi clinic in Überlingen. These participants will not receive any financial incentives. The recruitment started in September 2021. Thus, the last follow-up will be prospectively performed in January 2023. Study participants will be informed by email about their results and publications based on data collected in the GENESIS trial.

### Participants

Men and women aged 20–75 years with BMIs between 22 and 35 kg/m^2^ are eligible to participate if they match further eligibility criteria, as listed in Table 1. Any contraindication to fasting, as defined in the guidelines of fasting therapy including kidney, liver or cerebrovascular insufficiency (43) automatically leads to exclusion. Fulfilment of additional criteria related to contraindications for the MRI/MRS scans is required for participants of the MRI subgroup (Table 1).

**TABLE 1 T1:** Eligibility criteria.

Inclusion criteria	Exclusion criteria
• Men and women • Age between 20–75 years • BMI between 22–35 kg/m^2^ • Negative COVID-19 test • Available written declaration of consent	• Intake of medication (cardiovascular diseases, lipid, and glucose metabolism) • Chronic manifest psychical and psychiatric diseases • Participation in another study • Pregnancy or breastfeeding • Active uncontrolled gastrointestinal disorders including ulcerative colitis, Crohn’s disease, indeterminate colitis, severe irritable bowel syndrome, persistent infectious gastroenteritis, persistent or chronic diarrhea of unknown etiology, and recurrent *Clostridium difficile* infection • Major surgery of the gastrointestinal tract, in the past 5 years. Any major bowel resection at any time • Intake of antibiotics in the last 2 months • In the MRI subgroup, any MRI contraindication (claustrophobia, pacemakers, MR-incompatible prosthetic valves, metallic implants, and foreign metallic body)

### Fasting intervention

The subjects will receive a plant-based, organic calorie-restricted diet (600 kcal/day) 1 day before the study begins. The 12-day fasting period will be initiated by emptying the intestinal tract *via* the intake of a laxative [e.g., sodium sulfate (Glaubers’ Salt) in the morning or sodium picosulfate (Laxoberal^®^, Sanofi-Aventis, Germany) the night before]. During the fasting period, the energy intake is limited to 200–250 kcal/day (10), which will be achieved with 0.25 L freshly squeezed, organic fruit juice at noon, 0.25 L vegetable soup in the evening and 20 g honey. Participants will be asked to drink a minimum of 2 L of water or non-caloric, caffeine-free herbal teas that are purchased by certificated, organic companies (SONNENTOR Kräuterhandelsgesellschaft mbH, Sprögnitz, Austria; Ulrich Walter GmbH, Diepholz, Germany). Every second fasting day, the colon will be emptied by an enema or a laxative. On the last fasting day, plant-based organic food will be progressively reintroduced over 3–4 consecutive days (800–1,600 kcal/day).

Medical doctors and nurses will supervise the fasting intervention. An accompanying program consisting of physical exercise, mindfulness, and meditation will be provided and group interaction will be favored. The training program includes daily outdoor walks of 1.5 h, moderate-intensity fitness exercises and free access to the gym and swimming pool.

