#### Sulfur signaling

To address the transsulfuration pathway, sulfur compounds (amino acids, thiosulfate, and H_2_S) will be analyzed in serum and urine at baseline, after three fasting days, at the end of fasting, as well as 1 month post food reintroduction (75).

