#### Clinical data

Clinical data (e.g., body weight, body-mass-index, systolic and diastolic blood pressure, and heart frequency) will be documented at baseline, during fasting and food reintroduction as well as 1 and 4 months afterward. The abdominal circumference will be measured before and after fasting. Changes in ketonuria, capillary ketonemia, and capillary blood glucose levels will be measured during the fasting period and food reintroduction. Nitrogen balance, measured in 24-h urine samples (15), will be determined at baseline and during the fasting and food reintroduction period in the MRI subgroup only.

A clinical standard laboratory blood profile will be measured in each blood sample, during the transition day and after fasting (10). Additional blood samplings will be obtained from the first 32 subjects after three fasting days as well as 1 month afterward.

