### Data analysis plan

The data of all clinical endpoints will be collected before and after 9 ± 3 fasting days. Demographic data and each participant’s medical history will be captured at baseline. The detailed timing of all measurements is shown in Table 2.

**TABLE 2 T2:** Summary of measurements.

	Before	Transition	Fasting days													Food reintroduction	+1 month	+4 months
Measurements	−5 to −2	−1	0	1	2	3	4	5	6	7	8	9	10	11	12			
Demographic data	x																	
Medical history	x																	
Anthropometric measurements	x	x	x	x	x	x	x	x	x	x	x	x	x	x	x	x	x	x
Vital signs	x	x	x	x	x	x	x	x	x	x	x	x	x	x	x	x	x	x
Blood sampling		x				x			x								x	
Capillary blood sampling	x	x	x	x	x	x	x	x	x	x	x	x	x	x	x	x		
First morning urine sampling			x			x			x								x	
24 h urine sampling	x		x	x	x	x	x	x	x	x	x	x	x	x				
MRI	x												x				x	
MRS P31 and H1	x												x				x	
Bioelectrical impedance analysis	x												x				x	
Quadriceps muscle ergometry	x												x				x	
Triaxial actigraphy	x		x	x	x	x	x	x	x	x	x	x	x	x			x	
Spiroergometry	x										x						x	
Stool sampling	x															x		
Visual scores: wellbeing, symptoms	x	x	x	x	x	x	x	x	x	x	x	x	x	x	x	x	x	x
Questionnaires and life style		x											x				x	x
Adverse events	x	x	x	x	x	x	x	x	x	x	x	x	x			x	x	x

Measurements only conducted in the first stage of this study (*n* = 32) are highlighted in blue.

Further, the Supplementary File contains a detailed description of the anthropometric data, vital signs, blood, urine and stool samples, the MRI and MRS acquisition protocols, bioelectrical impedance analysis, quadriceps muscle ergometry, triaxial actigraphy, and spiroergometry.

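### As printed, the urine baseline for the sulfur outcome is taken on day 0, after the restricted transition day, so the fasting and 1-month contrasts in urine can be biased in a direction that depends on the analyte

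*Protocol article*

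**What the plan says.** Protocol article, Fasting intervention: "The subjects will receive a plant-based, organic calorie-restricted diet (600 kcal/day) 1 day before the study begins". This is the Transition column (day -1) of Table 2. The same section opens the fast with a laxative, and one of its two examples, sodium picosulfate, is taken on the preceding night.

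Protocol article, Sulfur signaling, gives this schedule for the sulfur compounds: "analyzed in serum and urine at baseline, after three fasting days, at the end of fasting, as well as 1 month post food reintroduction".

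Protocol article, Data analysis plan, Table 2, as printed:
- "First morning urine sampling": days 0, 3, 6 and +1 month. There is no mark at -5 to -2 or at -1.
- "24 h urine sampling": -5 to -2 and days 0 to 11. There is no mark at +1 month.
- Blood sampling: days -1, 3, 6 and +1 month.
- MRI, MRS, bioelectrical impedance and stool: first mark at -5 to -2.

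Protocol article, Clinical data, confirms the day of the first blood draw: "A clinical standard laboratory blood profile will be measured in each blood sample, during the transition day and after fasting". On the later draws it adds: "Additional blood samplings will be obtained from the first 32 subjects after three fasting days as well as 1 month afterward". It also gives the 24-h collection its purpose: "Nitrogen balance, measured in 24-h urine samples (15), will be determined at baseline", in the MRI subgroup only.

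**The concern.** A baseline should describe the participant before the exposure under study. The 600 kcal day is part of the intervention package, and the day-0 urine follows it. Where picosulfate was taken the night before, the sample also follows the laxative. Serum and urine, which the sulfur outcome pairs, then have baselines on different days and possibly under different intake.

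Two contrasts depend on this baseline. The fasting contrast (days 3 and 6 against day 0) loses whatever part of the response has already taken place. The 1-month contrast carries the same shift with reversed sign, so a participant who has simply returned to the pre-study level would appear changed. Because the study is single-arm and pre-post, such an artefact could be read as a lasting effect of fasting on sulfur metabolism.

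**Working it through.** The plan gives no sample size, effect size or power for the sulfur outcome, so there is no stated figure to reproduce. The check has three parts.

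**1. Which urine sample is the sulfur baseline?**

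| Time point named for sulfur | First-morning urine | 24-h urine | Blood |
|---|---|---|---|
| Baseline | day 0 | -5 to -2 | day -1 |
| Three fasting days | day 3 | day 3 | day 3 |
| End of fasting | day 6 (last mark in the fast) | to day 11 | day 6 (last mark in the fast) |
| 1 month | yes | no | yes |

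Only the first-morning row has a 1-month sample, and it runs parallel to the blood row. The inference is that it carries the sulfur outcome, with day 0 as baseline.

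**2. Form of the bias.** For one analyte, let D be the true change from habitual state to fasting, f the share of D already present at day 0, and L any true lasting effect at 1 month, with D and L in SDs of the paired difference. Relative to the habitual level, day 0 is at fD, fasting at D and 1 month at L.
- Measured fasting change = D - fD = (1 - f)D.
- Measured 1-month change = L - fD. With L = 0 this is -fD, opposite in sign to the fasting effect.

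An analyte that falls with restriction gives a false increase at 1 month; one that rises gives a false decrease. The only direction in the documents is in the Introduction, where fasting is said to raise H2S production and restriction to have raised H2S in mice. On that premise the H2S artefact is a false decrease. If the one-day response runs against the fasting response (f below 0), the fasting change is overstated instead.

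**3. Size, under assumptions.**

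Energy step. Habitual intake is not stated; 1,800-2,400 kcal/day is assumed. The fast is 200-250 kcal/day. The share of the step taken on the transition day is (habitual - 600) / (habitual - fasting):
- Smallest: (1,800 - 600) / (1,800 - 200) = 1,200 / 1,600 = 75%.
- Largest: (2,400 - 600) / (2,400 - 250) = 1,800 / 2,150 = 84%.

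This is energy only. It is not f.

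False 1-month finding. Inputs: two-sided paired t test, alpha 0.05, n = 32 (the first-stage group), no true lasting effect, assumed baseline shift in SD of the paired difference.

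| Shift (SD) | Chance of p < 0.05 |
|---|---|
| 0 | 5.0% |
| 0.1 | 8.5% |
| 0.2 | 19.5% |
| 0.3 | 37.6% |
| 0.4 | 59.2% |
| 0.5 | 78.2% |

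Fasting contrast. Inputs: D = 0.59 and n = 28, borrowed from the muscle triglyceride calculation under Sample size calculation for illustration only; f assumed.

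| f | Measured change (1 - f) x 0.59 | Power | 1-month bias, absolute size f x 0.59 |
|---|---|---|---|
| 0 | 0.59 | 85% | 0 |
| 10% | 0.53 | 77% | 0.06 |
| 20% | 0.47 | 67% | 0.12 |
| 30% | 0.41 | 56% | 0.18 |
| 50% | 0.30 | 33% | 0.30 |

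With a baseline before the transition day f is 0: the full D is measured and the 1-month contrast returns to its nominal 5%.

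**The case against.** The strongest reply has four parts.

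*The link is inferred.* The Sulfur signaling section says only urine, and the article refers to a Supplementary File, not shown here, for sample details. The 24-h row has a -5 to -2 collection, and its stated use for nitrogen balance does not exclude others. This stands as a caveat. But the 24-h row has no 1-month sample, so using it as baseline would set a 24-h collection against a spot urine at 1 month. Either reading needs the baseline to be named.

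*The table may be damaged.* Blood and first-morning urine stop at day 6 although the text speaks of the end of fasting, and MRI has no 4-month mark although the text requires one. Column positions should therefore be confirmed. The blood baseline on the transition day is supported by the text; the day-0 urine rests on the table alone.

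*Day 0 is a defensible start for the fasting phase.* It follows a common, provided diet, and the stated aim concerns change during fasting. This has merit as a reason to keep the day-0 sample. It is no reason to do without an earlier one at a visit where 24-h urine is already collected.

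*Stronger readings go too far.* A reader might infer that the 1-month contrast will show a false increase; the documents do not establish this, and for H2S their own premise points the other way. A reader might infer that three quarters or more of the fasting response is lost; the 75-84% is energy, and the documents contain no urinary sulfur values, no protein content for the transition day and nothing that turns one restricted day into a share of a 12-day response. A reader might also take it that everyone is back on habitual diet with full reversal at 1 month; the plan measures dietary behaviour at that point and assumes no such thing. On all of these the objection is right.

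**Conclusion.** The point holds in a conditional form. As printed, the urine baseline for the sulfur outcome follows the restricted day, differs by a day from the serum baseline, and departs from the -5 to -2 baseline used for MRI, bioimpedance, stool and 24-h urine. If an analyte responds to that day in the direction of fasting, its fasting change is attenuated by the factor (1 - f) and its 1-month change is shifted by -fD.

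The size is unknown. An assumed shift of 0.2 to 0.3 SD would raise the chance of a false 1-month finding from 5% to about 20-38% with 32 participants, and an assumed f of 20-30% would lower illustrative power from 85% to 67-56%. These figures rest on assumed f and shift, a borrowed effect size, and the inferred link to first-morning urine. The matter concerns one matrix of a non-primary outcome. The primary MRI endpoint is unaffected. The change is worth making because it is cheap, not because serious bias has been shown.

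**What to change.** - In Sulfur signaling and Table 2, name the urine sample that serves as the sulfur baseline. Add a first-morning urine at the existing -5 to -2 visit and keep day 0 as a separate post-transition value.
- State that the day -1 blood is drawn before the first restricted meal.
- Reconcile the day-6 marks for blood and first-morning urine with the text's end-of-fasting sample.
- For participants already studied, base the urine fasting contrast on stored 24-h aliquots (-5 to -2, days 3 and 6), if they exist and the analytes are stable in them. Do not interpret 1 month versus day 0 in urine as a lasting effect.

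Cost: one extra urine cup at a visit already held and a few words in the protocol. For those already enrolled, the fasting contrast would use 24-h rather than spot urine. With no 24-h sample at 1 month, their 1-month urine contrast cannot be recovered, only left uninterpreted.

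### A permitted sulfate laxative falls between baseline and the on-fast thiosulfate and H2S samples, so a pooled rise cannot be attributed to endogenous production unless laxative type and timing are known and used

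*Protocol article*

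**What the plan says.** **Bowel emptying.** The Fasting intervention section opens the fast with a laxative and gives two examples, "sodium sulfate (Glaubers’ Salt) in the morning or sodium picosulfate". It states no amount and no rule for choosing between them. During the fast, "Every second fasting day, the colon will be emptied by an enema or a laxative"; the agent is not named there.

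**Sulfur outcome.** The Sulfur signaling section says that "sulfur compounds (amino acids, thiosulfate, and H_2_S) will be analyzed in serum and urine at baseline, after three fasting days", and also "at the end of fasting, as well as 1 month post food reintroduction". Its stated purpose is the transsulfuration pathway. Sulfate is not among the listed analytes.

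**Purpose.** The Introduction gives as background that "Another aspect of LF-induced metabolic effects is increased endogenous hydrogen sulfide (H2S) production", and then states the objective: "we will investigate the impact of LF on H2S-mediated signaling in humans". The fourth item under Aims is narrower: "we will determine whether persulfidation, which contributes to the maintenance of cellular oxidative functions, changes during fasting".

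**Design and analysis.** The trial is a "prospective, monocentric, single-arm interventional study using a two-stage design". The Statistical analysis section plans mixed models for repeated measures and names age, gender and baseline body weight as examples of confounders.

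**The concern.** With one arm, the effect of fasting on thiosulfate and H2S is read from the change within each person. Anything that begins between the baseline sample and the on-fast sample, and that can move the same analytes, is part of that change. A sulfate salt taken to open the fast is a permitted co-intervention of this kind: an outside source of sulfur, given inside the before-after window of a sulfur outcome whose background rationale is endogenous production.

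What is at stake is attribution. A pooled rise could be published as support for fasting-induced endogenous H2S when part of it came from the laxative. The article names nothing that would separate the two.

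**Working it through.** The article states no figure for this point: no sulfate amount, no expected change in thiosulfate or H2S, and no sample size for the sulfur outcome. So there is nothing to reproduce. The check is of the order of events, followed by an illustration on assumed inputs.

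**1. Order of events** (Table 2 as extracted, so columns may be displaced)
- Blood: day −1, day 3, day 6, +1 month.
- First-morning urine: day 0, day 3, day 6, +1 month.
- Opening laxative: at the start of the fast, in the morning for sodium sulfate.

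Baseline blood precedes the laxative. First-morning urine on day 0 can be taken to precede a dose given that morning. The day-3 samples follow it. The last on-fast sample sits at day 6 in the extracted table and at the end of fasting in the Sulfur signaling section. The point does not depend on which is meant, since both come after the opening step.

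**2. Which time point is most exposed.** The only sulfate intake the article names is the opening one, so day 3 is the nearest sample. Later samples are less exposed unless the every-second-day agent is also a sulfate, which the text neither states nor excludes.

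**3. Who has the data.** The Clinical data section gives the extra blood samples after three fasting days and at 1 month to the first 32 participants. I infer that the day-3 sulfur contrast rests on about 32 people.

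**4. Sulfate load (assumed amounts only).** Amount of sulfate = mass / molar mass. For an assumed 10 to 40 g of the decahydrate (322.2 g/mol), 10/322.2 = 31 mmol and 40/322.2 = 124 mmol. This does not convert into a change in thiosulfate or H2S, because the fraction absorbed or reduced is unknown.

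**5. Could the laxative alone produce a significant rise?** Let p be the share who took sulfate and e the exogenous shift in takers, in SDs of the paired change. Assume no endogenous change.
- Pooled mean change = p × e
- SD of the pooled change = √(1 + p(1 − p)e²)
- One-sample t-test, n = 32, two-sided alpha 0.05

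Example with p = 0.5 and e = 0.5: mean 0.25, SD √1.0625 = 1.031, standardised shift 0.243, probability of significance 0.265.

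| Share taking sulfate | e = 0.5 SD | e = 1.0 SD |
|---|---|---|
| 25% | 0.103 | 0.242 |
| 50% | 0.265 | 0.688 |
| 75% | 0.520 | 0.965 |
| 100% | 0.782 | 1.000 |

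With no exogenous shift the figure would be 0.05. Neither p nor e is in the article. The table shows what could happen, not what will.

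**The case against.** **The laxative is part of the programme.** Bowel emptying is described under Fasting intervention with the juice, soup and exercise, so the before-after change is a fair estimate of the effect of that programme. This stands. The difficulty begins only when the change is credited to endogenous production.

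**Recording and covariates belong to documents not shown.** The article mentions case report forms, a study diary and a supplementary file, and its confounders are examples, not a closed list. This also stands: a reader might infer that the agent is not recorded or will not be modelled, but the article does not say so. The point rests on what the article does state, an unfixed agent that may be a sulfate and that falls inside the contrast.

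**The biochemistry is assumed.** It is. The article does not discuss oral sulfate as a source of H2S, and a dose given to empty the bowel may largely pass through. Size cannot be claimed.

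**Stronger readings that the documents do not support**
- *The trial sets out to show increased endogenous H2S.* That sentence is background. The stated objectives are H2S-mediated signaling, the transsulfuration pathway and persulfidation.
- *A rise can never be read as endogenous.* Sodium sulfate is one option. Participants given another agent would offer an internal comparison if the choice is known.
- *Participants received a mix of agents, or repeated sulfate.* Both are possible; neither is stated.
- *The whole fourth aim is compromised.* Nothing shows that the laxative alters persulfidation or the sulfur amino acids.

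**Conclusion.** The point holds for thiosulfate and H2S. A pooled rise over baseline, most of all at fasting day 3, cannot be attributed to endogenous H2S production unless laxative type and timing are known and used in the analysis.

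It rests on two assumptions: that gut bacteria can turn part of an oral sulfate load into H2S that reaches the measured analytes, and that at least some participants with sulfur measurements took sodium sulfate. Sodium picosulfate is counted here as a non-sulfate agent, on the further assumption that the sulfur it carries is negligible.

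The size is unknown. Over the assumed range in the table, the chance of a significant rise from the laxative alone runs from 0.10 to 1.00. This is a limit on interpreting a secondary mechanistic outcome. The primary MRI body-composition endpoint and the sample size are untouched.

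**What to change.** 1. For participants with sulfur measurements, capture the agent, amount and date of every bowel-emptying step, from existing records if needed.
2. As a sensitivity analysis, add sulfate exposure (yes/no) and its interaction with visit to the thiosulfate and H2S models. Report the estimated change with its interval separately for those with and without a sulfate agent. Time since last sulfate is not a useful substitute: with a single opening dose it coincides with visit in every taker.
3. If all or nearly all received sulfate, state the result as the change under the whole fasting programme, not as endogenous production.

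No change to the bowel-emptying rule is proposed.

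**Cost.** One data item, one model term with its interaction, and possibly a narrower claim. The comparison is not randomised and will be imprecise. In units of the SD of the paired change, the 95% half-width for the mean change in non-takers is 2.131/√16 = 0.53 if there are 16 of them and 2.365/√8 = 0.84 if there are 8. For the taker versus non-taker difference it is 2.042 × √(1/16 + 1/16) = 0.72 with 16 and 16, and 2.042 × √(1/24 + 1/8) = 0.83 with 24 and 8. A laxative contribution of 0.5 SD could therefore often not be excluded. For the same reason, the endogenous reading should not be made to depend on a significant rise in the non-sulfate subset, which could reject a true effect for lack of numbers.
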